## Abstract

**Background:**

While a number of preventive interventions delivered within schools have shown both short-term and long-term impact in epidemiologically based randomized field trials, programs are not often sustained with high-quality implementation over time. This study was designed to support two purposes. The first purpose was to test the effectiveness of a universal classroom-based intervention, the Whole Day First Grade Program (WD), aimed at two early antecedents to drug abuse and other problem behaviors, namely, aggressive, disruptive behavior and poor academic achievement. The second purpose--the focus of this paper--was to examine the utility of a multilevel structure to support high levels of implementation during the effectiveness trial, to sustain WD practices across additional years, and to train additional teachers in WD practices.

**Methods:**

The WD intervention integrated three components, each previously tested separately: classroom behavior management; instruction, specifically reading; and family-classroom partnerships around behavior and learning. Teachers and students in 12 schools were randomly assigned to receive either the WD intervention or the standard first-grade program of the school system (SC). Three consecutive cohorts of first graders were randomized within schools to WD or SC classrooms and followed through the end of third grade to test the effectiveness of the WD intervention. Teacher practices were assessed over three years to examine the utility of the multilevel structure to support sustainability and scaling-up.

**Discussion:**

The design employed in this trial appears to have considerable utility to provide data on WD effectiveness and to inform the field with regard to structures required to move evidence-based programs into practice.

**Trial Registration:**

**Clinical Trials Registration Number**: NCT00257088

## Background

The educational sector, as a normative setting for children, is an important delivery system for drug abuse prevention. A number of preventive interventions directed at aggressive, disruptive behavior and other antecedent risk factors such as poor achievement have shown both short-term and long-term impact in epidemiologically-based randomized field trials. However, prevention programs are often not implemented with high quality in schools [1-3]. Until recently, the primary concern of prevention researchers has been to test the impact of interventions through efficacy and effectiveness trials. The result is that many interventions have been tested without precise specification of the model of support necessary to implement and sustain intervention practices with high quality over time.

In fall 2003, we began the third randomized field trial carried out by the senior members of this research team in collaboration with the Baltimore City Public School System. This trial focused on testing interventions aimed at aggressive, disruptive behavior and poor achievement, separately and in combination. Results of the first two trials [4-15] provided support for undertaking this trial in which we combined three intervention components--classroom-behavior management; academic instruction, particularly in reading; and family-classroom partnerships--into one integrated intervention called the Whole Day First Grade Program (WD). This trial was designed to bring together effectiveness and implementation research. The design supported an effectiveness trial of the WD compared with the standard school district program (SC). The design also supported an examination of the utility of a multilevel structure to support high levels of implementation during the effectiveness trial, to sustain WD practices across additional years, and to train additional teachers in WD practices. This paper presents the implementation portion of the protocol in which we followed teachers with subsequent cohorts of children to study sustainability and scaling-up. Also see Additional File 1: 'Description of WD intervention, student sample, and measures of student outcomes' and Additional File 2: 'WD cohort two student sample figure'.

### Specific aims and hypotheses

The specific aim and hypotheses regarding implementation (aim three) follow logically from the aims of the effectiveness trial (aims one and two).

#### Aim one

Model the malleability of developmental paths by evaluating the effectiveness of the WD program, directed at reducing the antecedent risk factors for later substance abuse, comorbid mental and behavioral disorders, and school failure. We hypothesize that students in WD classrooms will exhibit less aggressive, disruptive behavior, more on-task behavior, and gains in student achievement, particularly in reading, compared with their counterparts in SC classrooms over the course of first grade and to the end of third grade.

#### Aim two

Measure the variation in the impact of WD by examining moderating factors at the level of the child and the social contexts of family, classroom and school, peers, and community. In line with the results from our previous trials, we hypothesize that: the impact of WD will be stronger among children who begin first grade with lower readiness and poorer student behavior than their classmates; and the impact of WD will vary as a function of the quality of teacher practices, with improved teacher practices leading to student improvements in behavior and achievement, proximally and through third grade.

#### Aim three

Examine the utility of the support structure: during the effectiveness trial; as teachers implement WD in consecutive cohorts of first graders (sustainability); and as WD practices are taught by school system employees to teachers new to WD (scaling-up). We hypothesize that: the multilevel support structure will result in sustained high levels of WD practices with three consecutive cohorts of first graders; and the multilevel support structure will result in high levels of WD practices with additional teachers when they are trained in WD practices.

## Methods

### Overview of the design

The within-school design involved 12 public elementary schools and two first-grade classrooms within each school. Within each school, three consecutive cohorts of children were randomly assigned to first-grade classrooms as they enrolled. Classrooms/teachers were randomized to intervention condition in the first year, with one teacher assigned to WD and one teacher assigned to SC. Because every school had a WD and a SC classroom, schools served as blocking factors, and comparison of intervention effects could be obtained for each school. This two-level randomized block design allowed us to hold school, family, and community catchment area factors fixed while examining intervention effects at the classroom level, and examine main effects and test hypothesized variations in impact on the basis of variables such as gender, students' individual aggressive behavior, teacher self-efficacy, and classroom levels of aggressive behavior. Random assignment of children to classrooms allowed two classrooms within a school to be comparable at baseline and was extremely efficient in testing the main effect of a classroom intervention [5,6,16,17].

Aware of the possibility of intervention leakage with this classroom-based, within-school design, we implemented procedures that had successfully limited such leakage in the prior trials, such as meeting with principals monthly [16]. In addition, the SC teachers received training and support in WD as part of the design in the third year of the trial. We found no evidence of contamination in the schools with internal controls in either of the first two trials [5,16] or in this trial.

### Procedures for random assignment

We drew upon our prior experience as well as knowledge in the field to develop protocols for the random assignment of both students and teachers. Here, we describe the procedures for random assignment in this multilevel trial. For details regarding the effectiveness arm of the trial in which we followed students over first grade and into third grade, see Additional File 1: 'Description of WD intervention, student sample, and measures of student outcomes' and Additional File 2: 'WD cohort two student sample figure'.

### Schools

We began with a pool of 66 elementary schools in two adminstrative areas of the school district. Schools were excluded if all the students attending the school received special education or other special services; the school was operated by an entity other than the school system; the first-grade curriculum was not the standard district curriculum; or the school had fewer than two or more than five first-grade classrooms. We excluded large schools because they were less common and tended to have different organizational structures than smaller schools. Twenty-six of the 66 schools were excluded as a result of these criteria. Because academic achievement was a primary target of the WD intervention, we decided that the schools performing less well academically would be eligible to be part of the WD initiative. The 40 schools remaining after the first exclusion step were ranked by third-grade academic achievement on the standardized achievement test used by the school system, third grade being the lowest grade at which a standardized achievement test was used to rate student achievement. In October 2002, principals of the 20 lowest performing schools participated in a lottery draw to randomly assign schools to participate either as one of eight schools deemed development schools, where we piloted intervention components and conducted staff training on assessment procedures, or as one of 12 schools deemed trial schools, where the randomized field trial would take place (see Figure 1). The trial was conducted in these 12 schools for three consecutive school years beginning in 2003 to 2004.

**Figure 1 F1:**
[figure not shown]
**WD Teachers Over Three Years**. R = random assignment; WD = Whole Day First Grade Program classroom; SC = standard classroom (control); SY = school year.

### Classrooms/teachers

In April 2003, all 37 first-grade classrooms/teachers in the 12 schools participating in the randomized field trial were randomly assigned to condition. In each school, one teacher was randomly assigned to be a WD classroom/teacher, one was randomly assigned to be a wait-listed SC classroom/teacher, and all other first-grade teachers were randomly assigned to be nonparticipating classrooms/teachers. Teachers in both WD and SC classrooms were followed as they taught three consecutive cohorts of first graders. In a type of wait-listed control, SC teachers who served as controls for cohorts one and two were trained in the third year to deliver WD to cohort three first-grade students. The effectiveness trial relied on efficient within-school comparisons of WD and SC for cohort one and cohort two students from first to third grade. The sustainability question centered on whether WD teachers' practices remained high or fell off across the three cohorts. The scale-up question centered on whether the practices of the former SC teachers improved--as well as the consequent child outcomes--when they were trained to deliver WD.

While each of the 12 schools maintained the design by having one WD classroom and one SC classroom each year for three years, there were changes at the teacher level as teachers left the school. We anticipated that some teachers would change over the years, and we established a protocol for such changes. We stipulated that if a teacher left, the classroom would not change condition and the new teacher would be assigned the departing teacher's intervention status. If the replacement was a teacher already in the school, our protocol stipulated that this teacher could not have previously been assigned to a condition (WD or SC) within the trial. The patterns of teacher mobility are shown in Figure 1. There were no changes in either WD or SC teachers in schools one to five; the same teachers taught the WD and SC classrooms for all three years of the trial. Schools six to 12 experienced some degree of teacher mobility.

Overall, the changes were typical of staffing in large urban school districts and a reality when conducting research in real-world settings. For example, in schools seven and eight, the original SC teacher stopped teaching during the first year of the study and a long-term substitute taught for the remainder of the year. In the second year of the study, these classrooms were assigned a permanent teacher who taught first grade in both the second and third years of the study. Of note is the fact that in the second year, school six had two SC classrooms. After the initial assignment of students to classrooms, the school decided to add a third first-grade classroom because enrollment was greater than anticipated. Because we did not have an established protocol for the situation, we worked with the school to determine appropriate actions to maintain the random design. We randomly selected 10 students to come out of the original WD and SC classrooms before the intervention began, creating a new control classroom. The teacher of this newly formed classroom did not have experience teaching first grade and was not trained in the school system's first-grade curriculum, so the original SC class and the new control classroom were combined in a team-teaching model. By the end of the year, these two classes had separated back into two traditional, discrete classes. We decided to collect data in all three classrooms at each time point throughout the year. As a result, we have one WD classroom and two SC classrooms for school six in the second year of the trial. In the third year, school six had only two first-grade classrooms and they were taught by the initially assigned WD and SC teachers. In spite of this unexpected design modification, we were able to maintain random assignment of children.

Although there were no instances of protocols being broken--no teachers changed their design--it is important to note that SC teachers were replaced at twice the rate over the three years of the study (n = 8) compared with WD teachers (n = 4). We have hypothesized that as teachers gain mastery in their classroom with regard to their practices in classroom behavior management and instructional content, they will be less likely to leave a school or the teaching profession. In keeping with this hypothesis, we would expect to see a lower rate of attrition in WD classrooms than in SC classrooms. As we move to an analysis of the data, we will test for systematic bias at the level of the classroom and at the school/community level.

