### Statistical power

In cohort one, we expect to have power of 0.79 to test the WD main effect on end-of-first-grade reading when the true effect size is 0.25, compared against total variation in the sample. This calculation is based on specification of multivariate means, variances, and covariances from data from prior trials conducted in Baltimore. The prior studies provide estimates of each source of variation as well (children, classrooms within schools, and schools) [70]. It assumes that individual variation is twice as large as school variation, that classroom variation at the time of randomization was negligible, and that the variation in intervention impact by school is a third of the overall variation, with effect size. Because this earlier trial involved a smaller number of schools (nine instead of 12 schools) and a less comprehensive intervention compared with that in the present trial, we anticipate having higher statistical power than in the previous trial. In that trial, we were able to report significant main effects and interactions [10,16]. The power is nearly identical for third-grade main effect analyses as it is for end-of-first-grade analyses, even when we allow for 20% attrition, primarily from mobility. This loss in power through attrition is generally more than offset by the increase in power from growth curve analysis [61].

For testing whether the intervention improved teacher practices, statistical power is slightly higher, for the same size effect, compared with analyses of child outcomes. This difference occurs because the teacher measures are not subject to the added statistical error arising from child variation. Thus, we expect to have sufficient power to detect moderate size effects in this trial on teacher practices across cohorts. Our hypotheses state that the WD effects on the original WD teachers should increase from cohort one to cohorts two and three. We plan to test this with a two-level linear trend model across cohorts. A test for nonlinear trend (one DF) can also be carried out. The trend tests are expected to have higher power than our original tests of sustainability because there should be stronger improvements of these teachers over the cohorts.

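### Scale-up and trend analyses are worded on original teachers, a group selected after randomization; the own-comparison power statement cannot hold for all 12 SC teachers, and a bias test is weak protection

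*Protocol article*

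**What the plan says.** All places are in the protocol article.

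- *Classrooms/teachers*, design: "each of the 12 schools maintained the design by having one WD classroom and one SC classroom each year for three years". Schools one to five had no teacher change; schools six to 12 had some.
- *Classrooms/teachers*, replacement rule: when a teacher leaves, "the classroom would not change condition and the new teacher would be assigned the departing teacher's intervention status".
- *Classrooms/teachers*, losses: over three years SC teachers were replaced 8 times and WD teachers 4 times. In schools seven and eight the original SC teacher stopped during year one. A long-term substitute finished that year, and a permanent teacher took years two and three.
- *Classrooms/teachers*, explanation: as teachers gain mastery of their practice, "they will be less likely to leave a school or the teaching profession", so lower attrition is expected in WD.
- *Classrooms/teachers*, handling: "we will test for systematic bias at the level of the classroom and at the school/community level". The variable tested and the consequence of a result are not given.
- *Analyses for Aim three*: scale-up compares the original SC teachers in their last year with their earlier years and with WD teachers. Power is expected to be similar to cohort one because each teacher is their own comparison. The sustainability sentence refers only to WD teachers, without the word original.
- *Statistical power*: power is 0.79 for cohort-one reading at effect size 0.25. Separately, "the WD effects on the original WD teachers" should grow from cohort one to cohorts two and three, tested with a two-level linear trend.

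**The concern.** The article's own theory links staying both to assigned condition and to quality of practice. Quality of practice is what Aim three measures, and Aim three is the focus of the paper. Original teachers still in post in year three are therefore not the randomized group, and the two arms may be thinned by different amounts and for different reasons.

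Three things are at stake. Practice among WD stayers may not describe practice in the 12 WD classrooms. The scale-up contrast has fewer same-teacher pairs than its power statement implies. And a non-significant bias test on so few classrooms could be given more weight than it can bear.

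**Working it through.** **1. The stated ratio.** With 12 classrooms per arm, (8/12) / (4/12) = 2.0, which reproduces the article's twofold rate. These are counts of replacements, not of classrooms.

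**2. How many classrooms changed.** Five schools had no change, so at most 12 − 5 = 7 SC classrooms can have changed teacher. School six had its initially assigned teachers in year three, so the likely maximum of SC classrooms that lost their original teacher is 6. On the WD side, 4 replacements touch at most 4 classrooms.

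**3. How many original SC teachers can be their own comparison.**
- Certain minimum: 5 (schools one to five); 6 if school six is counted.
- Certain maximum: 12 − 2 = 10, because the teachers in schools seven and eight never reached year three.
- Assumed upper value: if no changed classroom had more than two of the 8 replacements, at least 8/2 = 4 changed, leaving 12 − 4 = 8.

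**4. Power with fewer pairs.** Assumptions: two-sided 5% paired t test (the article gives no alpha), and power 0.79 with 12 teachers, taking the statement of similar power at its word. Power = 1 − F(t₀.₉₇₅,ⱼ₋₁), where F is the noncentral t distribution with J − 1 degrees of freedom and noncentrality d√J. Setting power to 0.79 at J = 12 gives d = 0.877. Holding d fixed:

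| Teachers J | d√J | Critical t | Power |
|---|---|---|---|
| 12 | 3.04 | 2.20 | 0.79 |
| 10 | 2.77 | 2.26 | 0.70 |
| 8 | 2.48 | 2.36 | 0.57 |
| 7 | 2.32 | 2.45 | 0.50 |
| 6 | 2.15 | 2.57 | 0.41 |
| 5 | 1.96 | 2.78 | 0.33 |

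**5. What a bias test could show.** The test is not described, so these are examples of classroom-level tests with 12 v 12.
- Classrooms changed, Fisher exact two-sided: 7/12 v 4/12 gives p = 0.41; 6/12 v 4/12 gives p = 0.68. If the 4 WD replacements fell in only 2 classrooms, 7/12 v 2/12 gives p = 0.09.
- Power against a true 7/12 v 4/12 difference: 0.15 (Fisher) or 0.23 (normal approximation).
- Power to detect a difference in a teacher covariate (two-sample t, 22 degrees of freedom, noncentrality δ√6): 0.22 at δ = 0.5 SD and 0.65 at δ = 1.0 SD.

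**6. Direction of stayer bias.** This is a simulation with no true effect. Quality and leaving correlate 0.3 to 0.5, weaker teachers leave, and the mechanism is the same in both arms (all assumed). With 4 of 12 WD teachers lost, the WD stayers' mean is about 0.15 to 0.26 SD above that of all 12. With 6 or 7 SC teachers lost, the SC stayers' mean rises more, so WD minus SC among stayers shifts by about −0.07 to −0.18 SD, against WD. If stronger teachers leave, the signs reverse.

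**The case against.** **The inheritance rule already protects the trial.** It does so for Aim one, which compares WD and SC within schools for cohort-one and cohort-two students and is not limited to original teachers. A reader might infer that the effectiveness result is compromised; the wording does not support that. If WD keeps teachers in post, lower turnover is arguably part of the effect of assignment. The sustainability sentence is not restricted to original teachers either.

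**Original may mean only first-assigned condition**, since both arms deliver WD in cohort three. This is a fair reading, and the word is ambiguous. But the same section uses it for the initially assigned person in schools seven and eight. If replacements are included, the own-comparison argument fails wherever the teacher changed between the years compared. The permanent teachers in schools seven and eight, who taught SC in year two and were there for year three, can be their own comparison without being original. Some correction is needed on either reading.

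**The bias test is undescribed, and a condensed article may leave it so.** This stands against saying that the test cannot find bias: a large imbalance could be detected. Nor does the article say that a non-significant result would be taken as clearance. What stands is that low power makes such a result uninformative.

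**Eight SC replacements might be read as eight of 12 classrooms.** That is impossible, because only seven schools had any change.

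**School six.** A reader might infer that its two SC classes in cohort two will count as independent clusters. The article says that "the original SC class and the new control classroom were combined in a team-teaching model" and that data were collected in all three rooms, but it does not say how they will be clustered.

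**Conclusion.** The point holds for the scale-up contrast and the trend hypothesis. As worded, both rest on a group defined by an event after randomization that the article itself ties to condition and to the outcome. The statement that each teacher is their own comparison, with power similar to cohort one, cannot be true of all 12 original SC teachers; at least two had left in year one. Under the assumptions above, power falls from 0.79 to about 0.33 to 0.57 with 5 to 8 teachers, and is still only 0.70 at the ceiling of 10.

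The direction of bias is not established. A reader might infer that stayer analyses must favour WD. They may overstate the level of sustained WD practice if weaker teachers leave, but the WD minus SC difference among stayers can move either way.

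The planned bias test is weak protection, not a useless step. No shift in the reading effect is claimed, because the article gives no figure from which one could be derived.

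**What to change.** 1. Make the primary Aim three analyses of practices and child outcomes, both the sustainability trend and scale-up, use all 12 WD and 12 SC classrooms as randomized, with replacement teachers under inherited status as the article's own rule provides.
2. Define *original*. Report same-teacher analyses as secondary, stating how many teachers contribute in each arm and cohort. They still answer the separate question of growth in teachers who stay.
3. Restate the own-comparison and power sentence to match: the classroom is its own comparison in the primary analysis, and the teacher only in the secondary one, with power given for the actual number.
4. Supplement the bias test with estimates of how far the effect moves in fixed sensitivity analyses applied to both arms: one addressing schools with any SC or WD teacher change, and one treating school six's team-taught SC classes in cohort two as a single cluster. Omitting schools by teacher change itself conditions on a post-randomization event, so these should be read as sensitivity estimates only.

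Cost: a few extra model runs on data already collected. The sustained-practice estimate may look less favourable because new teachers are included.
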